## Abstract

**Background:**

Patients with lymphoma are at risk of experiencing adverse physical and psychosocial problems from their cancer and its treatment. Regular screening of these symptoms by the use of patient-reported outcomes (PROs) could increase timely recognition and adequate symptom management. Moreover, self-management interventions intend to enhance knowledge and skills and empower patients to better manage their disease and related problems. The objective of the Lymphoma InterVEntion (LIVE) trial is to examine whether feedback to patients on their PROs and access to a web-based, self-management intervention named *Living with lymphoma* will increase self-management skills and satisfaction with information, and reduce psychological distress.

**Methods/design:**

The LIVE randomised controlled trial consists of three arms: (1) standard care, (2) PRO feedback, and (3) PRO feedback and the *Living with lymphoma *intervention. Patients who have been diagnosed with Hodgkin lymphoma, non-Hodgkin lymphoma, including chronic lymphocytic leukaemia, as registered in the Netherlands Cancer Registry in various hospitals will be selected for participation. Patients are invited via their haemato-oncologist 6 to 15 months after diagnosis. The PRO feedback includes a graphical overview of patients’ own symptom and functioning scores and an option to compare their scores with those of other patients with lymphoma and a normative population of the same age and sex. The *Living with lymphoma *intervention is based on cognitive behavioural therapy components and includes information, assignments, assessments, and videos. Changes in outcomes from baseline to 16 weeks, 12, and 24 months post intervention will be measured. Primary outcomes are self-management skills, satisfaction with information, and psychological distress. Secondary outcomes are health-related quality of life, illness perceptions, fatigue, and health care use.

**Discussion/design:**

The results of the LIVE trial will provide novel insights into whether access to PRO feedback and the *Living with lymphoma *intervention will be effective in increasing self-management skills and satisfaction with information, and reducing distress. The LIVE trial is embedded in a population-based registry, which provides a unique setting to ascertain information on response, uptake, and characteristics of patients with lymphoma in web-based intervention(s). When effective, PRO feedback and *Living with lymphoma *could serve as easily and widely accessible interventions for coping with lymphoma.

**Trial registration:**

Netherlands Trial Register, identifier NTR5953. Registered on 14 July 2016.

**Electronic supplementary material:**

The online version of this article (doi:10.1186/s13063-017-1943-2) contains supplementary material, which is available to authorized users.

## Background

Due to advances in treatment, the 20-year prevalence of Hodgkin lymphoma (HL) and non-Hodgkin lymphoma (NHL) in the Netherlands is expected to increase by 5% to 6300 and 32,000 patients in 2020, respectively [1, 2]. As a result of their cancer and its treatment, patients with lymphoma are at risk of experiencing adverse physical and psychosocial problems, such as fatigue, neuropathy, and cognitive and emotional problems [3–6]. Patients who report adverse problems have a lower health-related quality of life (HRQoL) and visit their physician more often [7–9]. In addition, up to a quarter of patients with lymphoma experience persistent levels of anxiety, depressive feelings, and fears, also called psychological distress [7, 10].

Patient-reported outcomes (PROs) intend to evaluate the impact of a disease and its treatment from the perspective of the patient [11]. PROs are being increasingly recognised to be important in daily practice [12, 13]. Regular screening of physical and psychosocial symptoms by the use of PROs could increase awareness and recognition of symptoms and can contribute to adequate symptom management [11, 14–17]. Moreover, the greater the resources available for coping with symptoms and stress, the lower the risk for psychological distress [18]. Interventions using cognitive behavioural therapy (CBT) components, such as psychoeducation and coping skills, can reduce persistent psychological distress and physical problems and improve HRQoL [8].

As the number of patients surviving lymphoma continues to grow, interventions need to be easily accessible without increasing the burden on health services. Self-management interventions can be effective in strengthening the role of patients, by increasing patient engagement in care, and limiting the burden on health services [19, 20]. Self-management interventions aim to empower patients to have an active role in the management of their disease and its symptoms and consequences including treatment, physical, and psychosocial and lifestyle changes [21, 22]. Web-based technologies are particularly suitable for self-management interventions since they are easily accessible, can reach a large number of patients [19, 23], and provide more anonymity compared to face-to-face interventions [24]. Therefore, web-based interventions have the potential to eliminate barriers to psychosocial care for patients with cancer. However, it is important that such interventions should be evidence-based and empirically tested [25].

The Lymphoma InterVEntion (LIVE) trial consists of two interventions: (1) feedback to patients on their PROs, and (2) a web-based, self-management intervention named *Living with lymphoma*. Patients will be randomised to: (1) standard care, (2) standard care plus access to PRO feedback or (3) standard care plus access to PRO feedback and the Living with lymphoma intervention. PRO feedback enables patients to monitor their symptoms and compare them with outcomes among other patients. This may help to either reassure that what they experience is ‘normal’ or may empower them to take action. The *Living with lymphoma *intervention is based on CBT components and is an adaptation from the evidence-based BREAst cancer e-healTH (BREATH) intervention [26]. By using the *Living with lymphoma* intervention, patients will receive psychoeducation and learn coping skills which they can apply as self-management skills in daily life.

## Methods/design

### Objectives and hypotheses

The objective of the LIVE trial is to examine whether PRO feedback and the* Living with lymphoma *intervention will increase self-management skills and satisfaction with information and reduce psychological distress. In concordance with the stress-coping model of Lazarus and Folkman (1984), psychological adjustment after cancer is determined by the balance between stress and resources [18]. Therefore, it is hypothesised that patients with access to PRO feedback and/or the *Living with lymphoma *intervention will report increased self-management skills and satisfaction with information (greater resources available for coping), and lower levels of psychological distress compared to patients receiving standard care. Moreover, it is expected that patients with access to both PRO feedback and the *Living with lymphoma *intervention will benefit most.

### Study design

The LIVE trial is designed as a nonblinded randomised controlled trial with three arms. For an overview of the design of the trial, see Fig. 1. Standard care plus the access to PRO feedback and the *Living with lymphoma *intervention (arm 3) will be compared to standard care plus access to PRO feedback (arm 2) and standard care (arm 1). Patients with lymphoma from various hospitals in the Netherlands will be included and asked to complete questionnaires at four points in time: baseline (T0; 6 to 15 months after diagnosis), after 16 weeks (T1; post intervention), after 12 months (T2), and after 24 months (T3).

**Fig. 1 Fig1:**
[figure not shown]
Overall study design of the Lymphoma InterVEntion (LIVE) trial

### Study population

All patients who have been diagnosed with HL or NHL, including chronic lymphocytic leukaemia (CLL), as defined by the International Classification of Diseases for Oncology-3 codes (ICD-O-3) [27], in the participating hospitals will be selected for participation via the Netherlands Cancer Registry (NCR). Patients must be aged 18 years or older at the time of diagnosis. Patients who have problems with the Dutch language, patients with severe psychopathology or dementia, and patients in transition to terminal care will be excluded from the study.

### Setting

The LIVE trial will be conducted within the Patient Reported Outcomes Following Initial treatment and Long-term Evaluation of Survivorship (PROFILES) registry [28]. PROFILES is a tool that enables data collection management; from inviting patients to participation in studies, to collecting PRO data via web-based or mailed questionnaires and linking these data with clinical data. Since this trial is embedded in the population-based PROFILES lymphoma registry, we have access to information on response, uptake, and user characteristics of patients with lymphoma in a web-based intervention.

### Recruitment

The population-based NCR of the Netherlands Comprehensive Cancer Organisation (IKNL) will be used to select all patients in the participating hospitals who meet the inclusion criteria. The NCR registers all newly diagnosed cancer patients within 6 months after diagnosis. After excluding deceased patients, the treating haemato-oncologists are asked to verify the patients’ study eligibility. All eligible patients will be invited for participation by their own haemato-oncologist. The haemato-oncologists will provide the eligible patients with an invitation package, including an invitation letter and leaflet to inform them about the study, a postcard, and two Informed Consent Forms (i.e. one for the researchers and one for the patient). The letter explains the study objectives and includes a link and password to a secure website so that patients can complete questionnaires online. If patients prefer paper-and-pencil participation, they can complete the postcard and return it by mail to the study manager. Patients will then receive paper-and-pencil questionnaires and a pre-stamped envelope within 1 week of receipt of the postcard. Patients are informed that paper-and-pencil participation automatically means that they will not be able to participate in the LIVE trial and only participate in the observational PROFILES lymphoma registry, as both PRO feedback and the Living with lymphoma intervention are web-based.

If the questionnaire is not completed within 3 weeks, a reminder will be sent by the treating haemato-oncologists. After obtaining informed consent, the subsequent communication to the patients will be addressed via PROFILES. To guarantee anonymity, questionnaires only contain a study number.

### Randomisation

Patients who complete the baseline questionnaire online and consent to participate in the LIVE trial will be automatically randomised in an equal ratio (1:1:1) to one of the three study arms: (1) standard care, (2) standard care plus access to PRO feedback or (3) standard care plus access to PRO feedback and the *Living with lymphoma *intervention. This randomisation will be performed using block randomisation. The randomisation will be performed by a computer randomisation program which will ensure a balance in sample size across groups over time [29].

### Interventions versus standard care

#### Arm 1: Standard care

For patients randomised to arm 1, the haemato-oncologist provides standard care. Most haemato-oncologists give their patients leaflets regarding the diagnosis and treatment they receive. Most information is given during the initial treatment phase, and some of the haemato-oncologists give additional information during follow-up for ad hoc referrals if needed by the patient. Patients who receive standard care can use information about lymphoma on the Internet, but do not have access to PRO feedback or the *Living with lymphoma *intervention.

#### Arm 2: PRO feedback

Patients randomised to arms 2 and 3 have access to PRO feedback, including general HRQoL, physical, emotional, cognitive and social functioning, fatigue, neuropathy (only for patients with high-grade NHL), and anxiety and depressive symptoms.

Patients can compare their scores to mean scores of other patients with lymphoma (same sex and age group) and/or a normative population (same sex and age group) to find out whether their scores are average or not (using a traffic light model). A detailed description of how to interpret the scores is added to assist patients in understanding the graphs. Mean scores of the lymphoma sample are extracted from data of our previous research on HRQoL among 856 patients with lymphoma [30]. The normative population was selected from a reference cohort of 1859 individuals from the general Dutch population (CentERpanel). This cohort is representative for the Dutch-speaking population in the Netherlands [31].

Individual scores will be integrated into graphical displays with coloured bar-charts [32, 33]. The colours of the bar-charts are related to clinically relevant mean differences of the evidence-based guidelines of the EORTC QLQ-C30 [34]. A score that differs less than the minimal medium clinically relevant difference from the mean score is considered ‘average’ (amber). A score that differs as much as or more than the minimal medium clinically relevant difference from the mean score is considered ‘above average’ (green) or ‘below average’ (red). The interpretation of anxiety and depressive symptoms is according to the published scoring algorithm: 0–7 indicating no or mild symptoms (green), 8–10 indicating moderate symptoms (amber), and ≥11 indicating severe symptoms (red) [35]. Patients with a score in the red part of the chart are advised to contact their general practitioner. For an example of PRO feedback, see Fig. 2.

**Fig. 2 Fig2:**
[figure not shown]
An example of patient-reported outcome feedback

To review the PRO feedback, patients have to click on the ‘feedback’ tab after completing the questionnaire. Patients can decide not to review their PRO feedback as they prefer not to.

#### Arm 3: PRO feedback plus *Living with lymphoma* intervention

In addition to PRO feedback, patients randomised to arm 3 get access to the* Living with lymphoma* intervention. This web-based self-management intervention is an adaptation of the evidence-based BREATH intervention for breast cancer survivors [26, 36]. The content of the intervention is adapted to warrant its relevance for patients with lymphoma. Symptoms that are typically common in patients with lymphoma, such as neuropathy, infections, and infertility, have been added.

One key feature of the intervention is the ‘work space’ that includes four phases: (1) ‘looking back’, (2) ‘emotional processing’, (3) ‘strengthening’, and (4) ‘looking ahead’. For a screenshot of the ‘work space’, see Fig. 3. The intervention is based on CBT techniques, such as psychoeducation, to enhance patients’ knowledge and skills, for instance by providing tailored advices based on patients’ input. Working ingredients of the four phases include information, assignments, assessments, and videos. The information part provides patients with knowledge on various subjects such as adverse physical and psychological problems, work, sexuality, and lifestyle. Assignments are, for example, writing tasks, social engagement or conversation tasks and aim to increase skill-building [26]. Assessments include tests that could be used by patients as a screening instrument of potential problems and are followed by automated feedback. Videos are clips extracted from recorded interviews with patients with lymphoma.

**Fig. 3 Fig3:**
[figure not shown]
Screenshot from the ‘work space’ of the *Living with lymphoma* intervention with phase structure (in Dutch)

Another feature of the intervention is the library with background and additional information on subjects from the four phases (e.g. work, sexuality, lifestyle). For a screenshot of the library, see Fig. 4. The library also contains links to additional health care services (e.g. psychologists, physiotherapists, dieticians).

**Fig. 4 Fig4:**
[figure not shown]
Screenshot from the library of the *Living with lymphoma* intervention (in Dutch)

The advised intervention usage is one part per week, with a duration of approximately 1 h. However, it is up to the patients how, and to what extent, they use the intervention. From the BREATH intervention it is known that patients use the website quite diversely [37]. The intervention is fully automated and nonguided and is delivered without the professional support of a therapist. Support for content or technical assistance is available by the study manager.

### Study outcome measures

Patient demographics and clinical information will be available from the NCR that routinely collects data on, among other things, patients’ age and sex, date of cancer diagnosis, histological classification, stage, treatment, and comorbidity. Information on marital status, educational level, and employment status are gathered by self-report using questionnaires.

#### Primary outcomes

*Self-management skills* are measured by the Health Education Impact Questionnaire (heiQ^TM^) [38]. The heiQ^TM^ contains 40 items across eight scales: positive and active engagement in life, health-directed activities, skill and technique acquisition, constructive attitudes and approaches, self-monitoring and insight, health service navigation, social integration and support, and emotional distress. Each item will be scored on a four-point Likert scale. The scale scores are obtained by computing the mean of respective items. Higher scores indicate better status or self-management, except for emotional distress, in which higher scores indicate higher distress [38]. The heiQ^TM^ has high construct validity [38]. Five scales of the heiQ^TM^ are validated among patients with cancer [39].

*Psychological distress* will be assessed by the 14-item Hospital Anxiety and Depression Scale (HADS) [35]. A sum score is obtained by adding the items. Its rating system is based on a four-point format and asks how the patient has felt in the past week. Higher scores indicate higher levels of psychological distress. The HADS has shown good reliability and validity in oncology settings [40, 41].

*Satisfaction with information* will be measured by an adapted version of the 9-item Information Satisfaction Questionnaire (ISQ) [42]. The ISQ has been widely used to assess overall information satisfaction and the need for involvement in decision-making. The original measure requires patients to categorise themselves into one of three groups: those who would like (1) all available information and to be involved in decisions about their illness, (2) only positive information about the illness, and (3) only limited information and would prefer the doctor to make the decisions. However, Fallowfield suggests that there is a distinction between the desire for information and involvement in decision-making [43]. Therefore, we divided that question into two items, one assessing the desire for information and one assessing the desire for involvement in decision-making. Patients are, furthermore, asked to rate their level of satisfaction with the information that they have received about their illness, treatment, and lifestyle. Each of these questions will be scored on a five-point Likert scale. The English version of the ISQ was translated into Dutch by forward-backward translation procedures. Questions about desire for more or less information, helpfulness of information, and the use of the Internet (to search for information) were added to the questionnaire.

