### Sample size calculation

Sample size calculation was performed using G*Power version 3.1.9.2 for Windows. Based on the three primary outcomes of this trial, effect on patient level is defined as increased self-management skills or satisfaction with information (as measured by the heiQ^TM^ and the ISQ, respectively) or reduced psychological distress (as measured with the HADS). Therefore, effectiveness of LIVE is demonstrated when one of the three effects is statistically significant. Significance level of the sample size calculation was adjusted to *p* ≤ 0.167 to keep the overall chance for type-I errors at 5%.

Clinically important differences will be determined with Norman’s ‘rule of thumb’, whereby a difference of approximately 0.5 SD indicates a threshold of discriminant change in quality of life scores of a chronic illness [59]. To detect a clinically important difference with 90% power, a sample size of 222 patients with lymphoma (74 in each group) is needed. This sample size calculation is based on a medium effect size of 0.25 for repeated measures analysis of variance (ANOVA) with two measurements, since at least two measurements are necessary to compare preintervention and postintervention outcomes. We take into account a response rate of 70% as observed in earlier studies (of them 60% are expected to complete the questionnaires online) and a study dropout rate of 25%, based on a systematic review on adherence to Internet interventions for anxiety and depression [60]. This results in 663 patients with lymphoma who need to be invited for participation.

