### Statistical analyses

All statistical analyses will be performed using Statistical Analyses Software (SAS; version 9.4 for Windows, SAS Institute Inc., Cary NC, USA). Analyses on effectiveness of the intervention will be primarily done according to intention-to-treat methodology. Second, per-protocol analysis will be performed to analyze the efficacy of the intervention. All statistical tests will be two-sided and considered significant if *p* < 0.05.

Missing outcome data will be assumed to be ‘missing at random’ (MAR), conditional on key predictors of ‘missingness’ (in particular, baseline values of the outcome variables of interest, and study arm).

Patients’ sociodemographic and clinical variables will be compared at baseline between the three study arms using chi-square analyses for categorical variables and ANOVA for continuous variables and will be analysed as covariates.

Repeated measures analysis using generalised estimating equations, which account for the intra-patient dependency of the repeated measures, will be used to analyse the effect of the intervention on the outcome variables. We will investigate differences in effect of the two intervention arms and the arm receiving standard care at the different time points. Differential effects of the intervention arms by age, cancer subtype, and baseline levels of the outcomes of interest will be assessed for the outcome measures by adding terms for the interaction between age, cancer subtype, baseline levels, and care arm to the regression models.

Routinely collected data from the population-based NCR on patient and tumour characteristics will enable us to compare paper-and-pencil respondents with online respondents, as well as respondents with nonrespondents and patients with unverifiable addresses in order to determine the external validity of the results and answer our second study objective.

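### The 5% overall error claim allows one test per primary outcome, but the heiQ and ISQ have no single deciding score, no contrast or visit is named, and the analysis section tests at an unadjusted 0.05

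*Protocol article*

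**What the plan says.** **Success rule and error claim.** Under Sample size calculation, the Protocol article states that "effectiveness of LIVE is demonstrated when one of the three effects is statistically significant". The three effects are increased self-management skills (heiQ), increased satisfaction with information (ISQ) and reduced distress (HADS). The significance level was "adjusted to *p* ≤ 0.167 to keep the overall chance for type-I errors at 5" per cent.

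**Scoring.** Under Primary outcomes, the heiQ "contains 40 items across eight scales", and "The scale scores are obtained by computing the mean of respective items". No total is defined. One of the eight scales, emotional distress, runs in the opposite direction to the others. For the ISQ, patients rate satisfaction with information on illness, treatment and lifestyle, and "Each of these questions will be scored on a five-point Likert scale". No composite is defined, and items on preferences for information and involvement sit alongside. Only the HADS is reduced to one number, a sum score.

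**Contrasts, visits and level.** Under Study design, arm 3 "will be compared to standard care plus access to PRO feedback (arm 2) and standard care (arm 1"), with follow-up at 16 weeks, 12 months and 24 months. Under Statistical analyses, "We will investigate differences in effect of the two intervention arms and the arm receiving standard care at the different time points", and "All statistical tests will be two-sided and considered significant if *p* < 0.05".

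**The concern.** Dividing 5% by three protects a rule with three tests. The outcomes as defined yield at least ten scores, and nothing in the article says which heiQ scale, which ISQ score, which pair of arms or which visit decides. The emotional distress scale adds a further difficulty. It belongs to the self-management instrument but is close in construct to the HADS, so distress could enter the success rule twice.

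The trial is nonblinded and its outcomes are self-reported. If the deciding scale were picked after the data were seen, no rule stated in the article would be broken, yet the result could be presented as meeting a criterion with 5% error. The analysis section also drops the three-way split, so the article gives two levels for the same tests.

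**Working it through.** **1. The plan's own figures.**
- A three-way split gives 0.05 / 3 = 0.0167. Three independent tests at that level give 1 - (1 - 0.0167)^3 = 4.9%, so the 5% claim holds for one test per outcome.
- The printed level is 0.167. Taken literally, 1 - (1 - 0.167)^3 = 42.2%. It appears to be a decimal slip.
- The sample size fits that reading. For the between-group test in a repeated-measures ANOVA (f = 0.25, three groups, two measurements, 90% power), the noncentrality is f² × N × 2 / (1 + ρ). At 0.0167 and ρ = 0.7, N = 222 with power 0.902. At 0.167, N is at most 144 for any ρ. The article does not state ρ, and 222 also follows from 0.05/6 with ρ = 0.5, so the match supports 0.0167 without proving it.

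**2. Counting scores.** Eight heiQ scales + one HADS sum + at least one ISQ score = 10. If the three ISQ satisfaction ratings are kept apart, the count is 12. Two intervention arms against standard care at three follow-ups would make it 10 × 2 × 3 = 60. That last step is the widest reading.

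**3. Error with independent tests.** For k tests at level α, any two-sided rejection has probability 1 - (1 - α)^k. A rejection in the direction of benefit has probability 1 - (1 - α/2)^k.
- k = 3, α = 0.0167: 4.9% two-sided, 2.5% benefit only.
- k = 10, α = 0.0167: 15.5% and 8.0%.
- k = 12, α = 0.0167: 18.3% and 9.6%.
- k = 3, α = 0.05: 14.3% and 7.3%.

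**4. Error with correlated tests.** The scores will be correlated, and the article gives no values. The figures below come from multivariate normal simulation under no effect: 40,000 runs, equal correlation between scores and between visits, and a shared control arm, so the two contrasts correlate at 0.5.

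| Reading | Level | Assumed correlation | Any two-sided | Benefit only |
|---|---|---|---|---|
| 3 scores, 1 contrast, 1 visit | 0.0167 | scores 0.3 | 4.7% | 2.3% |
| 10 scores, 1 contrast, 1 visit | 0.0167 | scores 0.7 to 0 | 8-15% | 4-8% |
| 10 scores, 2 contrasts, 3 visits | 0.0167 | scores/visits 0.7/0.7 to 0.3/0.6 | 31-51% | 16-27% |
| 10 scores, 2 contrasts, 3 visits | 0.05 | same | 62-86% | 33-53% |

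The benefit-only column matches the success rule most closely, because the article defines an effect as improvement.

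**The case against.** **The statistical analysis plan may settle this.** Naming the confirmatory scale, the contrast order and the primary visit is commonly left to that document, which is not shown, and the omission alone would be no finding. That stands. But the article itself publishes the any-one-of-three rule, the 5% claim and the p < 0.05 threshold, and these do not agree with the scoring set out beside them.

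**A reader might infer that any heiQ scale, in either arm, at any visit counts as success, so that the rule covers dozens of tests.** The article does not say so. It speaks of three effects, sizes the trial on one pre/post pair, and does not say that each visit triggers the success rule. With a single three-arm or arm-by-time test per score, the count is 10 to 12. The 60-test figures are therefore an upper reading.

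**Two-sided figures overstate the error of the stated rule.** This is right: they count significant harm as if it were success. Benefit-only figures are about half. On the narrowest reading, with score correlation near 0.7, the benefit-only error is about 4%, below 5%. It is still well above the 2.3% that three tests would give.

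**A reader might also see a contradiction in the arm contrasts.** Study design names 3 versus 2 and 3 versus 1, while the Discussion names each intervention arm versus standard care. Objectives and hypotheses covers all of these, so each section lists part of the set. That is incomplete listing, not conflict. What remains is that no contrast is named as decisive.

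**Conclusion.** The concern holds in this form: the 5% overall error is not secured by the plan as written. It requires one test per outcome at 0.0167, whereas the article defines at least ten scores, names no deciding score for the heiQ or ISQ, no contrast and no visit, and applies 0.05 in the analysis section.

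On the narrowest reading (10 scores, one contrast, one visit, 0.0167), the inflation is moderate: about 8-15% two-sided or 4-8% benefit only, against 4.7% and 2.3%. On the widest reading it is large: about 31-51% or 16-27% at 0.0167, and 62-86% or 33-53% at 0.05. The article does not commit to the widest reading, but does not exclude it either.

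The count of eight heiQ scales, the success rule and the two significance levels come from the article. The number of ISQ scores, all correlations and the reading of 0.167 as 0.0167 are assumptions.

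**What to change.** Before any analysis, and while the trial is still recruiting:

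- **One score per primary outcome.** One named heiQ scale other than emotional distress, chosen from the five that the article says are validated in patients with cancer (it does not list them, so the choice needs the cited source); the HADS total; and the mean of the ISQ satisfaction ratings.
- **One primary time.** T1 at 16 weeks, in line with the pre/post pair behind the sample size.
- **One decision per outcome.** Either a single three-arm test at T1 as gatekeeper to the pairwise contrasts, or a fixed order of contrasts, at 0.05 / 3 = 0.0167.
- **Consistent levels.** Correct the printed 0.167 under Sample size calculation, and apply 0.0167 to the primary tests under Statistical analyses.
- **Labels.** The other heiQ scales, the other ISQ items, T2 and T3 become secondary.

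The cost is an amendment to the wording, and results on those scales and visits become supportive. If pairwise contrasts replace the three-group test, the stated 90% power must be rechecked and restated. For a 0.5 SD difference with 74 per arm at two-sided 0.0167, 0.5 × √(74/2) - 2.39 = 0.65, which is about 74% power without baseline adjustment. With adjustment at an assumed baseline correlation of 0.5, 3.04 / √0.75 - 2.39 = 1.12, or about 87%.
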